### Procedure for unblinding if needed {17b}

N.A.

## Data collection and management

### Plans for assessment and collection of outcomes {18a}

A detailed overview of questionnaires and measures is given in Table 1. The schedule of enrolment, interventions, and assessments is provided in Table 2. Data management including data entry, coding, security, and storage will be provided by the Web-based application Research Electronic Data Capture **(**REDCap) 10.5195/jmla.2018.327 that is available at the University of Fribourg. It is Health Insurance Portability and Accountability Act (HIPAA)-compliant and highly secure.

**Table 2 Tab2:** Schedule of enrollment, interventions, and assessments

	From June 2021	> 1 day	> 2 days	After 8 weeks MORE intervention/waitlist	
Timepoint**	***-t***_***1***_	***t***^**0**^	***t***_***1***_	***T***_***2***_	***T***_***3***_
**Enrolment**	**Information screening**		**Pre-test measures**	**Post-test measurements**	**3-month follow-up**
**Eligibility screen**	**X**				
**Informed consent**	**X**				
**Baseline data**	**X**				
**Allocation**		**X**			
**Interventions**					
***F-DOPA PET scan***			**x**	**X**	
***MR scan***			**X**	**X**	
***Reward task***			**X**	**X**	
**Assessments**					
***Medical history*** ***Clinical psychiatric interview*** ***Physical examination, tender point evaluation*** ***Self-report scales***	**X**				
***Intervention related clinical outcomes***			**X**	**X**	**X**
***AA sampling***			**X**	**X**	

### Sociodemographic data

Data to be collected at baseline include age, sex, marital status, education level, and professional status. Measures of functioning include a measure of quality of life with the World Health Organization quality of life questionnaire WHOQOL Brief questionnaire [62] and the Fibromyalgia Impact Questionnaire-Revised (FIQ-R [7];) that also includes a measure of fatigue. Measures of sleep quality include the medical outcomes study sleep scale (MOS [63]; [44]) that has been widely used in rheumatology research and is recommended by OMERACT-10.

### Questionnaires

#### Pain-related outcomes

• *Pain severity and functional interference*: The Brief Pain Inventory (BPI) is used to obtain information on self-reported measures of pain severity and functional interference using the BPI [15]. Pain magnitude is queried by four items that ask about pain now, worst pain, least pain, and average pain. Items use numeric rating scales anchored by 0 (no pain) to 10 (most severe pain). Pain interference consists of seven items that ask about how pain interferes with aspects of daily living using numeric rating scales anchored by 0 (no interference) to 10 (completely interferes).

• *Current pain intensity*: The 1-item Verbal Rating Scale (VRS) from the SF-36 [70] is used to measure current pain intensity. The VRS has proven itself over decades as a valid, reliable, and change-sensitive measure of subjective pain [70].

• *Pain interference with functional impairment*: To measure the degree to which pain interferes with function in major life areas, we will use the 7-item Pain Disability Index (PDI) [18].

#### Other clinical measures

• *Severity of depressive symptoms*: To assess the severity of depressive symptoms, the Beck Depression Inventory (BDI)-II ([4, 43], a self-report questionnaire, will be used.

• *State and trait anxiety*: The State-Trait Anxiety Inventory (STAI) will be used as a measure of state and trait anxiety [48].

• *Mood states*: The Profile of Mood States (POMS) [53] will be used to assess transient, distinct mood states. The POMS measures six different dimensions of mood swings over a period of time with high sensitivity to change.

• *Quality of life*: To measure the quality of life, we will use the quality of life scale from the World Health Organization WHOQOL Brief questionnaire consisting of 26 items [62]. The WHOQOL Brief has good to excellent psychometric properties of reliability and performs well in preliminary tests of validity [68].

• *Function, impact, and overall symptoms of fibromyalgia*: The revised Fibromyalgia Impact Questionnaire (FIQ-R) [7] is a commonly used and validated 9-item instrument in the evaluation of fibromyalgia (FM) patients.

• *Sleep quality* will be assessed using the sleep quality, medical outcomes study sleep scale (MOS) [44, 63] that includes 12 items assessing sleep disturbance, sleep adequacy, somnolence, quantity of sleep, snoring, and awakening short of breath or with a headache.

• *Mechanisms underlying the MORE intervention*: For mechanisms related to the MORE intervention, we will assess with the following questionnaires: nonreactivity: Five Facet Mindfulness Questionnaire [2], the reinterpretation of pain sensations (Subscale of Coping Strategies Questionnaire, [11]), positive reappraisal (Subscale of Cognitive Emotion Regulation Questionnaire CERQ) [37], and savoring (Savoring Beliefs Inventory) [12], according to [26, 31]. They aim to understand the mechanisms related to the MORE intervention.

#### PET data acquisition

PET images will be acquired at the Department of Nuclear Medicine at the University Hospital Zurich. MRI overlay images will be acquired at 3 Tesla at the Department of Nuclear Medicine at the University Hospital Zurich, using T1-weighted sequence (MP-RAGE) to provide an anatomical framework for image analysis. 18F-DOPA is a well-validated measure of presynaptic DA function [45], and previous studies showed differences in 18F-DOPA binding between FM and healthy participants at rest [74, 75]. Subjects will have an intravenous catheter placed in their forearms. One hour before scanning, they will receive as routinely an oral dose of carbidopa 100 mg, a peripheral DOPA decarboxylase blocker and entacopone 400 mg, a peripheral catechol O-methyltransferase antagonist, and an additional 50 mg dose of carbidopa 30 min before 18F-DOPA injection in order to provide increased availability of 18F-DOPA for striatal uptake. The purpose of the premedication regimen is to limit the metabolism of the 18F-DOPA tracer by peripheral enzymes, i.e., DOPA decarboxylase and catechol O-methyltransferase, thereby maximizing central uptake [54]. Subjects will lay quietly before administration of the tracer to allow them to habituate into the environment and to relax. Subjects will then be injected with approximately 100 MBq of 18F-DOPA. Dynamic scanning will be performed up to 100 min after injection of tracer, but at least between 40 and 90 min after injection (cite https://www.ncbi.nlm.nih.gov/pmc/articles/PMC5584692/). Scans will be acquired on a PET/CT Discovery 690 scanner. Subjects will undergo the PET and MRI measures on the same day at the same place. Participants will have time to rest and to have lunch between both measures. PET measures will take place at pre-test and post-test. Pre-test measures take place 6 weeks to 1 day before the beginning of the MORE intervention. Post-test measures take place from 1 day after completion of the MORE intervention (i.e., + 8 weeks and 1 day after the beginning of the MORE intervention) to 6 weeks after completion of the MORE intervention (i.e., + 14 weeks after the beginning of the MORE intervention).

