### Participant timeline {13}

The overall study duration is 4 years from June 2021 to June 2025. Recruitment will take place during the entire study duration as we will perform 4 successive groups of the MORE intervention. The study duration per participant will be between 6 and 8 months, depending on scanner availability for the pre- and post-test measures. As soon as we have a minimum of 10 FM participants (minimum 5 participants and maximum 10 participants per MORE group), we will start with the first MORE group. The first measures will ideally be performed on healthy participants. The FM participants will be randomized after screening, and the ones assigned to the MORE intervention will undergo the pre-test measures of FM first. We plan 4 to 5 weeks to perform the pre-test measures for the participants allocated to the MORE group (2 participants per week). The first MORE will take place in the center where we will have first recruited the necessary number of participants. During the duration of the first MORE group (8 weeks), we will make the pre-test measures for the non-intervention control group and begin the pre-test measures for the second MORE group. This will allow us to begin with the second group as quickly as possible after the completion of the first group. During the second MORE group, we will perform the post-test measures for the first MORE group participants and test the non-intervention controls of the second MORE group. During fall 2021, we will test participants of the healthy control group and recruit the participants for the next two MORE groups that will take place in winter/spring 2022, according to a similar schedule for the first 2 groups. In parallel, we will perform the follow-up measures for MORE 1 and MORE 2. FM participants allocated to the non-intervention group will have the possibility to participate in a MORE group at the earliest after all participants of the group have completed follow-up measures, i.e., around 20 weeks after pre-test-measures (8 weeks delay for post-test measures + 12 weeks after post-test measures). In the years 2023 and 2024, we will complete the measures for the control group as well as the follow-up measures for the FM groups.

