## Assignment of interventions: allocation

### Sequence generation {16a}

We will use a simple randomization procedure with a blocked size of 5, 6, or 8 according to the recruitment flow. Randomization will be performed with an online program (sealed envelope, https://www.sealedenvelope.com) with the following randomization scheme: FMS MORE/FMS non-treatment control. The randomization will be performed for each group independently, before the pre-test measures by the data manager. Randomization tables will be deposited on RedCAP. There is no randomization of the healthy control groups for allocation in the PET or AA group.

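### MORE baselines are scheduled before the course and control baselines during it, so the group × time test of pain and clinical scales does not compare the same stretch of natural course in both arms

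*Protocol article*

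**What the plan says.** The section on PET data acquisition states: "Pre-test measures take place 6 weeks to 1 day before the beginning of the MORE intervention". It does not restrict this to an arm. The same section lets post-test run from 1 day to 6 weeks after the course, that is, up to 14 weeks after it began.

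The participant timeline ({13}) describes a different order: "The FM participants will be randomized after screening, and the ones assigned to the MORE intervention will undergo the pre-test measures of FM first". The MORE arm's pre-tests take 4 to 5 weeks at two participants per week. Then: "During the duration of the first MORE group (8 weeks), we will make the pre-test measures for the non-intervention control group". During the second course the plan is to "test the non-intervention controls of the second MORE group", and the next two groups run "according to a similar schedule for the first 2 groups".

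Sequence generation ({16a}) confirms that allocation comes before baseline: "The randomization will be performed for each group independently, before the pre-test measures by the data manager".

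Trial design ({8}) places the controls' T1 and T2 8 weeks apart. The timeline adds 12 weeks to follow-up, 20 weeks after pre-test. The section on follow-up measures gives the controls' follow-up as 20 to 24 weeks after MORE begins. The main analysis ({20a}) is a group × time ANOVA with pre-test and post-test as the time levels.

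**The concern.** A group × time test reads the difference in change between arms as the treatment effect. That requires the two arms' change scores to cover the same part of the natural course after allocation. Here the lag from allocation to baseline depends on the arm, because MORE women are measured first and controls later.

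If women enrol when symptoms are high and then drift back, with most of the drift early, more of that fall lies between T1 and T2 in the MORE arm. It would be credited to MORE. VRS and BPI are listed among the main primary outcomes ({12}), and unblinded participants report them themselves.

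**Working it through.** Weeks are counted from the start of the cohort's MORE course (week 0).

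**1. The plan's own figure.** Control follow-up after pre-test: 8 + 12 = 20 weeks, as stated. Throughput: 2 per week × 4 to 5 weeks = 8 to 10 women, which fits one MORE group.

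**2. Do the windows fit together?** Controls tested during the course have T1 at weeks 0 to 8.
- PET-section window for T1: week −6 to day −1. None of these controls meets it.
- Control T2 = T1 + 8 = weeks 8 to 16. A T1 after week 6 passes the +14-week limit; with even scheduling that is (8 − 6)/8 = 25% of them.
- Control follow-up = T1 + 20 = weeks 20 to 28. A T1 after week 4 passes the +24-week limit; with even scheduling, (8 − 4)/8 = 50%.

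**3. Offset between baselines** = mean control T1 − mean MORE T1. MORE pre-tests spread over the 4 to 5 weeks before the course have mean −2.0 to −2.5.
- Controls spread over weeks 0 to 8 (mean +4): offset 6.0 to 6.5 weeks.
- Controls in the first 4 to 5 weeks (mean +2.0 to +2.5): 4.0 to 5.0 weeks.
- Controls in the last 4 weeks (mean +6): 8.0 to 8.5 weeks.

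**4. Illustrative size.** Assumptions, none from the documents: allocation at week −5; an elevation e at allocation of 0.3 or 0.5 SD, decaying as e × 2^(−t/h), with t in weeks since allocation and half-life h of 4 to 12 weeks. MORE T1 is uniform on t = 0.5 to 5 and control T1 on t = 5 to 13. The mean share of the elevation left over a window a to b is h/[ln 2 × (b − a)] × [2^(−a/h) − 2^(−b/h)].

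Example, h = 6, both intervals 8 weeks: MORE 0.736 − 0.292 = 0.444; control 0.366 − 0.145 = 0.221; difference 0.223. Times 0.3 SD = 0.067 SD.

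With MORE T2 in the stated window (weeks 8 to 14, t = 13 to 19): MORE 0.736 − 0.161 = 0.575; difference 0.354. Times 0.3 SD = 0.106 SD.

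| h (weeks) | Equal intervals: share | × 0.3 to 0.5 SD | Stated MORE T2 window: share | × 0.3 to 0.5 SD |
|---|---|---|---|---|
| 4 | 0.307 | 0.09 to 0.15 | 0.401 | 0.12 to 0.20 |
| 6 | 0.223 | 0.07 to 0.11 | 0.354 | 0.11 to 0.18 |
| 12 | 0.095 | 0.03 to 0.05 | 0.235 | 0.07 to 0.12 |

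The equal-interval columns isolate baseline timing, but they put MORE T2 at weeks 3.5 to 8, before the course ends, so they do not describe the actual schedule. The right-hand columns use the stated window but also contain the effect of a longer MORE interval: mean T2 about +11.1 minus mean T1 −2.25 is about 13.3 weeks, against 8 in controls. Under strictly linear drift with equal intervals, baseline timing contributes nothing.

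**The case against.** The PET window is anchored to the start and end of MORE, which only one arm attends, and controls have an 8-week interval of their own. On that reading the window covers MORE women and the timeline covers controls. A reader might infer a plain self-contradiction, and the text does not quite support that. The controls' follow-up is nevertheless counted from the start of MORE, so the schedule stays unclear. The dependence of baseline timing on arm remains on either reading.

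The timeline says pre-test explicitly only for the first group's controls. For the second it speaks just of testing them, and for the rest of a similar schedule. That every control is affected, and by 6 weeks, is inference.

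The drift is assumed. Eligibility sets no minimum pain score, and a group starts only once at least 10 FM participants are available, so early recruits may already have waited. At 32 per arm with a change SD of 1, the standard error is √(2/32) = 0.25. A bias of 0.067 SD is then 0.27 standard errors and raises two-sided error to only about 5.8%; 0.153 SD gives about 9% and 0.20 SD about 12%. This stands: the effect may be small.

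A reader might also infer that post-test scans are non-concurrent between arms. They largely overlap: weeks 8 to 14 for MORE, about 8 to 16 for controls.

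**Conclusion.** The point holds as a scheduling fault that should be corrected. Time from randomisation to baseline differs systematically by arm, by about 4 to 8.5 weeks on average under plausible scan patterns. The stated windows for T1, T2 and follow-up cannot all apply to controls tested during the course.

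The direction favours MORE only if improvement is faster soon after enrolment. That is plausible for VRS, BPI and the clinical scales, but the documents do not show it. The range of 0.03 to 0.20 SD rests wholly on the assumed elevation and half-life, and its upper part includes the unequal interval. It should not be read as an estimate for this trial.

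A reader might extend the bias to 18F-DOPA influx, the only primary outcome named in the abstract. Nothing in the documents shows post-enrolment drift in that measure, so the point is confined to the self-reported outcomes.

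**What to change.** - Send VRS, BPI and the other online questionnaires to both arms of each cohort in the same week before the first session, and again in the same week after the last. They are completed at home and do not depend on the scanner. This removes the difference in baseline timing for these outcomes and makes the T1–T2 interval equal.
- Reconcile trial design ({8}), the participant timeline ({13}), the PET section and the follow-up section to one assessment schedule that states each window for each arm.
- Interleave MORE and control scans only as far as capacity allows. At 2 per week, 16 to 20 women need 8 to 10 weeks, more than the 6-week pre-test window, so full interleaving within it is not feasible.
- Do not rely on a covariate for weeks from allocation to T1. In the model above the lags do not overlap between arms (0.5 to 5 against 5 to 13 weeks), so it would be almost fully confounded with arm.

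Sending the questionnaires on common dates costs little. The drawback is that some controls' questionnaires will precede their scan by several weeks, which loosens the exploratory correlations between self-report and Ki unless the questionnaires are repeated at the scan. Ambulatory self-reports are tied to the week before or after the PET scan, so they keep the arm difference unless they are moved too.

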**Methods:**

The present study is a multi-center interventional RCT with 3 time points: before the intervention, after completion of the intervention, and 3 months after completion of the intervention. Sixty-four FM patients will be randomly assigned to either the MORE intervention (*N* = 32) or a non-intervention control group (*N* = 32). Additionally, a comparison group of healthy women (*N* = 20) for PET measures will be enrolled and another group of healthy women (*N* = 15) will do the ambulatory assessments only. The MORE intervention consists of eight 2-h-long group sessions administered weekly over a period of 8 weeks. Before and after the intervention, FM participants will undergo [18F] DOPA positron emission tomography (PET) and functional MR imaging while performing a reward task. The primary outcome will be endogeneous DA changes measured with [18F] DOPA PET at baseline, after the intervention (after 8 weeks for the non-intervention control group), and at 3 months’ follow-up. Secondary outcomes will be (1) clinical pain measures and FM symptoms using standardized clinical scales; (2) functional brain changes; (3) measures of negative and positive affect, stress, and reward experience in daily life using the ambulatory assessment method (AA); and (4) biological measures of stress including cortisol and alpha-amylase.

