## Trial design {8}

This is a multi-center interventional RCT with 3 time points: before the intervention (pre-test measures, T1), after completion of the intervention (post-test measures, T2), and 3 months after completion of the intervention (follow-up measures, T3). Participants in the non-intervention control condition will perform the T1 and T2 measures adjuvant 8 weeks apart. Study evaluation will be done by comparing within and between the groups. Healthy controls will perform T1 measures only. The potential effect will be assessed on a series of outcome measures (Table 1). Measures will take place at baseline T0, T1, T2, and T3.

**Table 1 Tab1:** Questionnaires at assessment (T0), baseline (T1), and 3-month follow-up (T2)

Variables	T0	T1	T2	T3	

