**Pain-related outcomes**					
Brief Pain Inventory (BPI, [15])		x	x	x	
Verbal Rating Scale for current Pain Intensity from SF-36 [70]		x	x	x	
Pain Disability Index [20]		x	x	x	

Before T1, we will perform the screening of the participants with regard to the inclusion and exclusion criteria (T0). Pre-test and post-test measures include each a 18F-DOPA PET scan at rest and a fMRI measure with the use of the reward task, the ambulatory assessment (AA) measures, the clinical and pain measures, and the fMRI measures. The follow-up consists in questionnaire assessments only, including the self-reported pain and clinical measures associated with PET and fMRI measures. The questionnaires will be presented through an online survey that is suitable for RCTs (Research Electronic Data Capture, RedCAP) and available at the Universities Fribourg and that can be filled at home.

The non-intervention FM control will undergo the same measures at pre-test and post-test, with a post-test planned on average after 8 weeks. They will not participate in any specific intervention, but will be given the opportunity to participate in MORE after the follow-up assessment (Fig. 1).

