
#### Follow-up measures

Follow-up measures include all questionnaires presented online via RedCAP, 3 months after the end of MORE intervention (+ 20 to + 24 weeks after MORE beginning for the non-intervention control group).

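### The planned pre-test to post-test interval is longer in the MORE arm than in controls, so the group-by-time contrast is partly confounded with elapsed time

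*Protocol article*

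**What the plan says.** For the MORE arm, the section PET data acquisition counts from the course. Before it: "Pre-test measures take place 6 weeks to 1 day before the beginning of the MORE intervention". After it: "Post-test measures take place from 1 day after completion of the MORE intervention", which the article gives as 8 weeks and 1 day from the start, and at the latest "to 6 weeks after completion of the MORE intervention (i.e., + 14 weeks after the beginning of the MORE intervention".

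For controls, four places give 8 weeks:
- Abstract, Methods: "after the intervention (after 8 weeks for the non-intervention control group".
- Trial design {8}: "Participants in the non-intervention control condition will perform the T1 and T2 measures adjuvant 8 weeks apart".
- Trial design {8}, text below Table 1: "with a post-test planned on average after 8 weeks". No window is given around this average.
- Participant timeline {13}: "8 weeks delay for post-test measures + 12 weeks after post-test measures", so about 20 weeks from pre-test to follow-up.

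The PET windows cannot simply be read as covering controls too. The participant timeline has the MORE women pre-tested first and the controls pre-tested while the course is already running.

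For follow-up, the section Follow-up measures gives "20 to + 24 weeks after MORE beginning for the non-intervention control group".

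The main analysis (Statistical methods {20a}) is a treatment group by time ANOVA with two nominal time levels, pre-test and post-test. It is used for 18F-DOPA influx and for the VRS and BPI pain scores, all listed as primary outcomes.

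**The concern.** The group-by-time term is read as the effect of MORE on change. That reading needs change to be measured over the same length of time in both arms. Here the schedule gives the MORE arm a longer interval, so anything that moves with time has longer to act there: the natural course of symptoms, season, permitted new treatments, or slow changes in measurement.

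Randomisation does not remove this, because the difference arises after allocation and because of it. Women are randomised before pre-test, and the arms then follow different calendars. The article neither aligns the two intervals nor says that the actual interval will be used in the analysis.

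**Working it through.** **1. The article's own figures reproduce.** Latest MORE post-test: 8 + 6 = 14 weeks from the start (98 days). Earliest: 8 weeks + 1 day = 57 days. Control follow-up: 8 + 12 = 20 weeks after pre-test.

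**2. Permitted MORE interval** = days from pre-test to course start + days from course start to post-test.
- Shortest: 1 + 57 = 58 days, or 8 weeks 2 days.
- Longest: 42 + 98 = 140 days, or 20 weeks.
- Planned for controls: 56 days. Excess in MORE: 58 − 56 = 2 days up to 140 − 56 = 84 days (12 weeks).

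**3. Likely mean excess.** The article does not say how the windows will be used, so each line rests on an assumption.
- Both windows used evenly: (1 + 42)/2 + (57 + 98)/2 = 21.5 + 77.5 = 99 days = 14.1 weeks. Excess: 6.1 weeks.
- Pre-tests confined to the 4 to 5 weeks of the participant timeline, post-test window used evenly: 14.5 + 77.5 = 92 days (13.1 weeks) to 18 + 77.5 = 95.5 days (13.6 weeks). Excess: 5.1 to 5.6 weeks.
- Two women per week, as the participant timeline plans for pre-tests, and the same rate assumed at post-test: the average group of 8 (Sample size {14}) needs 4 weeks on each side. Mean interval: about 2 + 8 + 2 = 12 weeks. Excess: 4 weeks. Groups of 5 and 10 give 1.25 + 8 + 1.25 = 10.5 and 2.5 + 8 + 2.5 = 13 weeks.

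For an average-sized group, the mean excess is therefore about 4 to 6 weeks.

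**4. What this could do to the test (illustration only).** The article gives no time trend. Assume a linear trend of 0.01 to 0.03 SD of the change score per week, of either sign. Bias = trend × excess:
- 4 weeks: 0.04 to 0.12 SD.
- 6 weeks: 0.06 to 0.18 SD.

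With 32 per arm, SE = √(2/32) = 0.25 SD. The chance of rejecting a true null at two-sided 5% is Φ(−1.96 + bias/SE) + Φ(−1.96 − bias/SE). This gives 5.3% at 0.04 SD and 11.1% at 0.18 SD. With no trend it stays at 5%.

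**5. Follow-up.** If controls are pre-tested in weeks 0 to 8 of the course, the participant timeline puts their follow-up at weeks 0 + 20 = 20 to 8 + 20 = 28. The section Follow-up measures says weeks 20 to 24. The two agree only in part.

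**The case against.** The strongest reply is that unlike things are being compared. The PET section gives outer limits, while the control figure is a planned average without a window. The participant timeline also says that time in the study depends on scanner availability, without limiting this to one arm. So single controls may well be measured later than 8 weeks. This stands, but it does not close the gap, because the planned control average lies below every permitted MORE interval.

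A reader might go further in several ways that the documents do not support:
- **That MORE's effect will be inflated by a stated share of the planned d = 0.5.** No trend of either sign is given. That effect size is cited for self-reported pain under secondary-outcome power, not for 18F-DOPA influx. Scanning up to 6 weeks after the last session could also dilute an effect.
- **That regression to the mean biases all primary outcomes.** Women are not selected on 18F-DOPA influx, so it does not obviously apply there. It is more plausible for pain.
- **That co-treatment runs free over the longer interval.** Section {11d} withdraws women who start dopamine-active drugs, regular psychotherapy or another trial before post-test. Other treatments remain allowed.
- **That controls are followed up too early.** With T2 at week 16, follow-up at weeks 20 to 24 would come only 4 to 8 weeks later. This needs the latest control pre-test and a literal reading of the MORE start for women who do not start MORE. It is ambiguous wording in a questionnaire-only visit outside the pre-post primary test.

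**Conclusion.** The concern holds as a scheduling asymmetry built into the plan. The pre-post interval is 8 weeks 2 days to 20 weeks in MORE against a planned average of 8 weeks in controls. The range is exact from the article's own windows. The mean excess of about 4 to 6 weeks rests on assumptions about scan booking.

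The primary contrast is therefore partly confounded with elapsed time. The documents do not show that a bias exists, how large it would be, or which way it would point. The illustrative trend rates are assumptions.

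A reader might infer that adjusting for the actual interval would settle the matter in the analysis. It would not. If controls stay near 8 weeks, the two distributions barely overlap, interval is nearly collinear with arm, and the adjustment would rest on extrapolation. The point is worth acting on because prospective scheduling removes the imbalance cheaply and later analysis cannot reliably do so.

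**What to change.** 1. Set one T1-T2 window for both arms. One way is to schedule control T2 so that, within each cohort, the control intervals have the same distribution as those of the MORE group. Individual pairing is not needed.
2. Reconcile the abstract, Trial design {8} (both places), Participant timeline {13} and PET data acquisition with that rule.
3. Define control T3 from the control's own T2, so that the participant timeline and Follow-up measures agree.
4. Record the actual T1-T2 and T2-T3 intervals and report them by arm. For women already measured, use the interval descriptively or in a cautious sensitivity analysis only.

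Cost: no extra scans. Controls wait longer for T2 and for their MORE place, and the section {11d} restrictions, which run until post-test, last longer for them. At the extreme, T2 at 20 weeks plus 12 weeks to follow-up is 32 weeks, beyond the 5 months of availability mentioned in the Discussion. If the change counts as substantial, section {25} requires ethics approval before it is put into effect.
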